## Abstract

**Background:**

The incidence of femoral neck fractures (FNFs) is increasing, primarily due to an aging population and an increased incidence of high-energy trauma. Although fixation with three cannulated screws (TCS) is the most commonly used surgical technique, it has limitations, including suboptimal operative accuracy and dependence on repeated intraoperative fluoroscopy. In response, advanced navigation systems have been developed to improve surgical precision and outcomes.

**Objective:**

This multicenter, prospective, randomized controlled superiority trial will compare surgical outcomes between an intelligent navigation system and the conventional freehand technique for FNF, as well as long-term fracture healing and complication rates.

**Methods:**

This multicenter, prospective, randomized controlled superiority trial will compare navigation system–assisted TCS fixation with conventional freehand TCS fixation in patients with FNF from June 2024 to October 2026. Eligible participants are adults aged ≥18 years diagnosed with FNF who are indicated for internal fixation. The primary outcome is the frequency of intraoperative fluoroscopy. Secondary outcomes include the neck-shaft angle, guide wire placement quality, operative time, intraoperative blood loss, fracture healing status, the Harris Hip Score, the 36-Item Short Form Health Survey, and the Zarit Caregiver Burden Score. The sample size calculation indicated that 150 (50%) participants per group (N=300) would be needed to detect a superiority margin of 15.4 fluoroscopy images with 80% power and a 1-sided α of .025, accounting for a 15% dropout rate. All patients will undergo 12 months of follow-up. Data analysis will compare groups using 1-sided *t* tests and Mann-Whitney *U* tests, supplemented by linear mixed-effects models with study site as a random effect.

**Results:**

The study was funded in May 2024 and received initial ethics approval from the institutional review board. Patient enrollment commenced in June 2024 and is projected to be completed by October 2026, with a target sample size of 300 participants. The final 12-month follow-up is expected to be completed by October 2027. As of manuscript submission, recruitment is ongoing, and no data analysis has been performed.

**Conclusions:**

Successful completion of this study may introduce a new strategy for the management of FNF and help establish a standardized protocol for the use of navigation systems, potentially enhancing clinical outcomes and reducing complication rates.

**Trial Registration:**

ClinicalTrials.gov NCT06713018; https://clinicaltrials.gov/study/NCT06713018

**International Registered Report Identifier (IRRID):**

DERR1-10.2196/88180

## Introduction

Hip fractures constitute a significant global health issue. They contribute greatly to morbidity, disability, and mortality, and they impose heavy demands on health care resources worldwide [1,2]. By 2050, the annual incidence of hip fractures is projected to rise to approximately 6.26 million. Almost half of these cases are expected to occur in Asia, particularly in China [3,4]. Each year, more than 1 million new femoral neck fractures (FNFs) are reported globally, with a rising incidence among younger populations [5]. The fixation of these fractures is inherently more technically complex. Despite advances in management, these fractures continue to be associated with a high complication rate. This can be explained by intrinsic factors, such as high-energy trauma and precarious vascularity, as well as iatrogenic contributors, including delays in diagnosis, imperfect fracture reduction, and insufficient fixation [6-8].

Reduction and internal fixation are the main treatments for FNF in young and middle-aged adults, typically using multiple cannulated screws or a dynamic hip screw [9,10]. However, a recent network meta-analysis of 33 randomized trials involving 5703 patients demonstrated that internal fixation carries substantially higher reoperation risks than arthroplasty (cannulated screws: odds ratio 9.98; dynamic hip screw: odds ratio 5.07) and yields inferior functional outcomes measured by the Harris Hip Score and the EQ-5D [11]. These findings underscore the importance of optimizing internal fixation techniques, particularly when femoral head preservation is desired. Most implants require precise guide wire positioning, traditionally achieved using a drill guide or alignment jig. In minimally invasive settings, achieving this precision without direct visualization is challenging, as poor positioning may cause malalignment and implant cutout [11-14].

A variety of advanced technologies, including orthopedic surgical robotic navigation, computer-assisted navigation systems, and intelligent minimally invasive visualization platforms, have been developed to enhance the precision and safety of cannulated screw placement and other implants procedures while reducing access morbidity and radiation exposure [12-14]. In the navigation system group, the first-pass success rate of TCS implantation reached 93.3%, compared to 60% in the freehand group, demonstrating a statistically significant difference (*χ*^²^=4.7; *P*=.03) [15]. According to a previous review, the primary success rate of other navigation systems ranged from approximately 93% to 99% in recent years, indicating a substantial improvement over freehand techniques [16-18]. Moreover, Schep et al [19] reported that a fluoroscopy-based navigation system achieved an accuracy of 1.17 mm, whereas Browbank et al [20] reported a precision of 3.4 mm for their X-ray–based mechanical guidance device. Therefore, a statistically significant and clinically meaningful reduction in fluoroscopy frequency would provide direct evidence of the navigation system’s superiority in terms of surgical efficiency and radiation safety [21].

Despite these innovations, current techniques, ranging from the conventional freehand approach to more technologically advanced solutions, still fall short of concurrently meeting the essential requirements of procedural simplicity, high accuracy, and minimal radiation exposure [22]. Some navigation systems have limitations, such as disruption of the conventional surgical workflow, increased operative time, and excessive preoperative imaging collection, which restrict their clinical application [23-25].

To address the aforementioned limitations, the StarNav-1 Orthopedic Surgical Navigation System was developed through an academic-industry collaboration between our research group and Visual MedTech Co, Ltd. This system effectively facilitates fracture reduction in long bone, periarticular, and spinal fractures. It is compatible with conventional internal implants, such as plates and intramedullary nails. It enables precise implantation with millimeter-level accuracy. It has obtained medical device registration in China. Preliminary cadaveric and sawbones validation studies have shown satisfactory outcomes. Preliminary unpublished data from the pilot phase demonstrated a reduction of approximately 15.2 fluoroscopy images per operation in the navigated group, with a first-pass guide wire success rate of 94.2%.

Building upon prior research, this multicenter, prospective, randomized controlled trial is designed to compare surgical outcomes between navigation system–assisted fixation and conventional freehand treatment for FNF, as well as the discrepancies in long-term fracture healing and complication rates. In this approach, the StarNav.1 Orthopedic Surgical Navigation System, provided by Visual MedTech Co, Ltd, will be used to guide implant positioning and fixation. The successful completion of this study will introduce a new strategy and establish a standardized protocol for the use of navigation systems in the management of these fractures.

## Methods

### Trial Design and Study Setting

This prospective, multicenter, randomized controlled clinical trial was designed to determine the superiority of the intervention. The study will take place at the Chinese People’s Liberation Army General Hospital and collaborating institutions from June 2024 to October 2026. Patients will be randomly allocated to 1 of 2 treatment groups (Figure 1): group 1—three cannulated screws (TCS) and group 2—navigation system–assisted TCS (NS+TCS).

**Figure 1 figure1:**
[figure not shown]
Overview of the participation in the clinical study. NS: navigation system; TCS: three cannulated screws.

### Description of the Novel Device

The navigation system primarily consists of a surgical planning workstation (laptop computer), a surgical navigation console, and a navigation instrument table. The entire setup has a minimal footprint and features user-friendly operation. The main procedural workflow proceeds as follows. First, anteroposterior and lateral views of the target lesion area are acquired, ensuring that all marker spheres of the image registration device and the target lesion area are included. Next, after determining whether distortion correction is needed based on the intraoperative use of a C-arm (equipped with a flat-panel detector or image intensifier), registration verification and trajectory planning for TCS are performed on the workstation system. This system enables simultaneous planning of all TCS, eliminating the need for repeated adjustments to optimize their spatial relationship and thereby reducing surgical time. Finally, guide wires are implanted along the planned trajectories, and subsequently, depth measurement and TCS insertion are completed (Figure 2).

**Figure 2 figure2:**
[figure not shown]
Main equipment of the navigation system.

It must be emphasized that although the novel navigation system can provide visual assistance for fracture reduction, manual reduction will be exclusively used in this study to minimize variability and potential bias, thereby safeguarding study quality. The navigation system will be primarily used for surgical planning and screw placement.

### Sample Size

The sample size was calculated using the following equations:

[figure not shown]

**(1)**

[figure not shown]

**(2)**

In these equations, 1–α denotes the significance level, *1–β* represents the statistical power, *Z_1−α_* and *Z_1−β_* are critical values derived from the Z-table, *σ* refers to the SD of the 2 groups, *δ* indicates the mean difference between groups, and *Δ* stands for the superiority margin.

According to published literature, the mean number of intraoperative fluoroscopies in screw fixation for FNFs is approximately 32.2 times [26], while the use of a navigation system is expected to significantly reduce fluoroscopy frequency. On the basis of preliminary pilot data and the experience with navigated procedures at our institution, the mean (SD) number of fluoroscopy images for the control group (nonnavigated) is 32.2 (SD 5.2), and that for the experimental group (navigated) is 15.2 (SD 3.7). The superiority margin was set at 15.4, with a 1-sided significance level of .025 and a statistical power of 0.8.

With a 1:1 allocation ratio between the 2 groups, the sample size calculation was performed using the aforementioned formula and PASS (version 15.0; NCSS LLC) software. Considering patient recruitment feasibility, each group required 126 participants, yielding a total of 252 subjects. After accounting for a 15% dropout rate and distribution across multiple centers, the final sample size was set at 150 (50%) per group, resulting in a total of 300 participants.

### Allocation

This multicenter trial will adopt a competitive enrollment model conducted concurrently at all participating sites. Initial participant distribution will strive for relative balance to ensure adequate representation across centers. As the study progresses, site-specific enrollment targets may be revised to maintain intercenter equilibrium, accounting for practical constraints and variations in recruitment rates. Centers recruiting fewer than 10 participants in either the control or experimental arm will be analytically grouped according to China’s geographic and demographic patterns. Sites contributing more than 50% of the total sample will be subject to investigator-stratified subgroup analyses.

### Randomization and Blinding

This is a single-blind trial in which patients and outcome assessors will be blinded to treatment allocation, while operating surgeons cannot be blinded because of the distinct intraoperative workflows associated with the navigation system and the freehand technique. Patients will remain blinded to their group assignment throughout the surgical procedure and the entire 12-month follow-up period, with the specific technique disclosed only after completion of all outcome assessments unless early unblinding is required for safety reasons. Radiographic assessors and functional outcome assessors will be blinded to group allocation, as all imaging studies and clinical assessments will be coded with unique participant identifiers and conducted without access to treatment assignment records. The primary statistical analyst will remain blinded until the final database is locked and all predefined analyses are completed, with group codes revealed only after the statistical analysis plan has been fully executed. Emergency unblinding may be performed by the principal investigator in the event of a serious adverse event for which knowledge of the intervention is essential for patient management, and any such event will be documented and reported.

Randomization will be performed by the coordinating center using a centralized computer-generated system with permuted blocks of 4 to ensure balanced allocation across treatment groups. Assignment details will be distributed to all participating sites via sequentially numbered, sealed opaque envelopes. All surgical procedures will be performed in accordance with the assigned randomization.

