#### Intervention Group: NS+TCS Fixation

Following successful anesthesia, the patient is positioned supine on a traction table. Satisfactory reduction of the fracture fragments is achieved under G-arm fluoroscopic guidance. The operative field is routinely prepared and draped in a sterile fashion.

Two guide pins are inserted, one at the anterior superior iliac spine and another at the lateral femoral condyle, to serve as anchoring points. A navigation reference array is then mounted. The exposed ends of the guide pins are trimmed to an appropriate length to avoid interference with subsequent fluoroscopic imaging. Image registration markers are positioned anteriorly and laterally to the hip joint. Standard anteroposterior and lateral hip radiographs are acquired and uploaded to the navigation system workstation for preoperative trajectory planning for TCS placement. An inverted triangular configuration is selected for dispersed screw placement. After calibration of the navigated drill sleeve, the planned trajectories are used to percutaneously insert 3 guide wires sequentially into the femoral neck and head through small skin incisions. Subsequently, TCS are inserted over the guide wires. Fluoroscopic confirmation is obtained to verify satisfactory screw length and position.

Upon confirmation of adequate fixation, the reference guide pins at the anterior superior iliac spine and lateral femoral condyle are removed. The surgical incisions are irrigated and closed in layers (Figure 3).

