**Clinical and imaging assessments**								
	Radiography	✓		✓	✓	✓	✓	✓
	Computed tomography scan	✓		✓			✓	✓
	Harris Hip Score	✓		✓	✓	✓	✓	✓
	36-Item Short Form Health Survey quality-of-life score	✓		✓	✓	✓	✓	✓
	Zarit Caregiver Burden Scale	✓		✓	✓	✓	✓	✓
	Local physical examination	✓		✓	✓	✓	✓	✓
	Rejection reaction		✓	✓	✓	✓	✓	✓
	Fracture healing				✓	✓	✓	✓
	Weight-bearing status				✓	✓	✓	✓
	Femoral neck shortening			✓			✓	✓
	Wound healing assessment			✓	✓			

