#### Informed Consent

Written informed consent will be obtained from every participant or a legally authorized representative before any study-related procedures are performed. All eligible patients will receive comprehensive information regarding the study purpose, procedures, potential risks and benefits, alternative treatments, and the voluntary nature of participation. Patients will be explicitly informed that refusal to participate or withdrawal at any time will not affect their subsequent medical care. Consent forms will be signed and dated by both the participant and the investigator obtaining consent. For patients with cognitive impairment who are unable to provide consent but meet the inclusion criteria, consent will be obtained from a legally authorized representative in accordance with local regulations.

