### Strengths and Limitations

This trial has several methodological strengths. The multicenter design enhances generalizability across different hospital settings. Prospective randomization with concealed assignment minimizes selection bias. Blinded outcome assessment for patients, radiographic reviewers, and functional assessors reduces detection bias. The sample size calculation was based on published literature [27] and a prespecified superiority margin, ensuring adequate power for the primary outcome.

Several limitations should be acknowledged. First, operating surgeons cannot be blinded because of the distinct intraoperative workflows associated with the navigation system and the freehand technique, which may introduce performance bias. However, the primary outcome is an objective, quantifiable measure that minimizes the impact of this bias. Second, the 12-month follow-up period may be insufficient to detect very late complications, such as osteonecrosis of the femoral head, which can occur beyond 1 year. Finally, all participating centers are in China, and findings may not be directly generalizable to health care systems with different surgical training practices or equipment.

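### Nothing described secures 12-month blinding of patients and functional assessors, because only the navigated arm has pin wounds away from the hip

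*Protocol article*

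**What the plan says.** Under Randomization and Blinding, the protocol article states that "Patients will remain blinded to their group assignment throughout the surgical procedure and the entire 12-month follow-up period". It adds that radiographic and functional assessors are blinded, because "all imaging studies and clinical assessments will be coded with unique participant identifiers and conducted without access to treatment assignment records". No other means of concealment is named.

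The two operations are described separately. Under Control Group: TCS Fixation, the skin wounds are three lateral hip incisions of about 1 cm each. Under Intervention Group: NS+TCS Fixation, "Two guide pins are inserted, one at the anterior superior iliac spine and another at the lateral femoral condyle, to serve as anchoring points". Their exposed ends are trimmed, and at the end of the operation "the reference guide pins at the anterior superior iliac spine and lateral femoral condyle are removed".

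Under Informed Consent, "All eligible patients will receive comprehensive information regarding the study purpose, procedures, potential risks and benefits, alternative treatments".

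The Follow-Up Visits section puts functional scoring and general health assessment at the scheduled outpatient visits. Table 2 ticks "Local physical examination" at every follow-up visit and a wound assessment at 2 weeks and 1 month.

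Under Strengths and Limitations: "Blinded outcome assessment for patients, radiographic reviewers, and functional assessors reduces detection bias". The only people named there as unblinded are the operating surgeons.

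**The concern.** Coding and restricted records conceal the arm from someone who works from files. They do not conceal a mark on the skin. The navigated arm has two wound sites that the control arm lacks, both away from the lateral hip incisions. Patients live with these wounds and have been told about the study procedures. An assessor who sees the limb uncovered may notice them.

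The Harris Hip Score and SF-36 rest on what patients report and, for Harris, also on what an assessor records. The SF-36 in particular is the patient's own account. If the arm can be inferred, a modest difference in favour of the new technology cannot be separated from expectation. The limitations paragraph defends the trial against bias by pointing to the objectivity of the primary outcome. That defence does not extend to these scores.

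**Working it through.** No figure in the plan depends on this point, so the check sets the relevant statements side by side.

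1. **What is claimed.** Patients are blinded through surgery and 12 months, and functional assessors are blinded (Randomization and Blinding; repeated as a strength under Strengths and Limitations).

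2. **How it is to be achieved.** Coded identifiers and no access to assignment records. This is a workable blind for someone reading coded radiographs. It says nothing about what is visible on the patient.

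3. **How the arms differ on the skin.**

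| | Control | Navigated |
|---|---|---|
| Lateral hip | three incisions of about 1 cm | small incisions for three guide wires |
| Anterior superior iliac spine | none described | one pin, removed at the end |
| Lateral femoral condyle | none described | one pin, removed at the end |

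The pins have exposed ends and carry the reference array, so they pass through the skin. Removing them leaves two wounds that the control operation does not produce. The article describes no sham mark, matched dressing or covering.

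4. **Who can see the difference, and when.** Patients can see it at any time. For others, Table 2 gives the exposure:

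| Visit | Local examination | Wound assessment | Harris and SF-36 |
|---|---|---|---|
| 2 weeks | yes | yes | yes |
| 1 month | yes | yes | yes |
| 3, 6, 12 months | yes | no | yes |

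The outcome definitions use 1, 3, 6 and 12 months. A local examination therefore falls at all four outcome visits, and a wound assessment at one of them. No rule is given on who examines and who scores, or in which order.

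5. **Which outcomes are exposed.** Harris and SF-36 rely on the blinding that is claimed. The Zarit score is answered by caregivers, for whom no blinding is claimed, so it is open to expectation in any case. The primary outcome is an intraoperative image count and cannot be changed by what is seen at follow-up. Neck-shaft angle, guide wire placement, operative time and blood loss are likewise untouched, and the coded imaging is not in question.

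6. **Whether a size can be given.** The document has no input from which to estimate a bias. The only arithmetic available is the smallest observed difference that reaches two-sided P<.05 at a single time point, with n per arm and the difference in SD units: 1.96 × √(2/n).
   - n = 150: 1.96 × √(2/150) = 0.226 SD
   - n = 126 (the plan's number per arm before its dropout allowance): 1.96 × √(2/126) = 0.247 SD

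   These are significance thresholds and say nothing about how large an expectation effect would be.

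**The case against.** The strongest reply is that this is a condensed article. Dressings, order of assessment and the choice of examiner are commonly left to a full protocol, which is not shown. The article does say that functional assessors are blinded, and its visit table lists activities without saying that the person who scores also examines the wounds. Nor does the consent section say that patients are told which pin sites belong to which arm.

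Much of this stands. A reader might infer that the blinding fails outright, or that nearly every patient's arm will be recognised. The documents do not support either reading. They give no rate of recognition, do not place the scorer at the wound check, and do not rule out concealment described elsewhere. The case is strongest for patients and weaker for assessors. A reader might also take 0.226 SD as the size of the bias, which it is not.

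What does not stand is that the point is only a missing detail. The article names its mechanism, and that mechanism cannot hide the wounds that the same article describes. It also lists the result as a strength and names surgeons as the only unblinded party.

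**Conclusion.** The point holds in a limited form: blinding of patients and functional assessors for the Harris Hip Score and SF-36 is not secured by anything the article describes. The unqualified statements under Randomization and Blinding and under Strengths and Limitations go further than the stated mechanism allows.

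The conclusion rests on two assumptions: that percutaneous pin sites leave marks visible for at least the early visits, and that no concealment is specified elsewhere. How long the marks stay recognisable, and how many patients or assessors would draw the right inference, is unknown.

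The consequence is confined to the interpretation of secondary functional and patient-reported outcomes. The sample size, the primary comparison and the main superiority conclusion do not change.

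**What to change.** **For the visits that remain**
- Have the functional assessor score before the local examination and wound check. Cover the hip and both pin sites in the same way in both arms, and leave the examination to the treating team.
- Ask the patient and the assessor for their guess of arm at 1 month. Read any later guess with caution, since it may reflect the perceived outcome as much as a loss of blinding.

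**In the text**
- Describe any concealment of the pin sites already in use.
- Qualify Randomization and Blinding and Strengths and Limitations to say that patient blinding may be compromised by the pin wounds.
- State that differences in Harris and SF-36 will be interpreted as potentially subject to expectation bias. Say the same for Zarit, for which no caregiver blinding is claimed.

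**Limits and cost.** Covering the sites and fixing the order protect assessors only; they cannot blind patients to their own wounds. For patients, the useful steps are the recorded guess and the qualified wording. Enrollment began in June 2024 and is due to end in October 2026, with follow-up to October 2027, so the new steps cover only patients still in follow-up, and many 1-month visits may already have passed. The text changes apply to the whole sample. The practical cost is coverings at scored visits, an order-of-assessment rule, and a guess-of-arm question for patient and assessor. The price is a weaker blinding claim.

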### Recruitment Strategy and Patient Screening

Before the study begins, baseline characteristics and medical history will be recorded for all potential participants. Those who meet the eligibility criteria (Textbox 1) will receive detailed study information, including the study purpose, procedures, risks, and benefits. Informed consent will then be obtained voluntarily. Eligible subjects who meet all criteria will be formally enrolled. They will then be assigned to treatment groups according to the site’s randomization scheme. After entering the electronic randomization system, all subject data will be locked. Each operation within the system will be automatically recorded in audit trails for monitoring purposes (Figure 1).

Eligibility criteria for the study.

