**Exclusion criteria**
Prior participation in another clinical trial within the period prior to the primary end point assessmentKnown allergy or hypersensitivity to ≥1 components of the implant materialsDeemed by the investigator to be medically unfit or too frail to tolerate the surgical procedure due to systemic comorbiditiesPresence of active infective foci in the hip or other parts of the body, as determined by the investigatorDiagnosis of metabolic bone disease, radiation-induced bone disease, or similar conditionsSevere hip contracture or significant muscle weakness with long-standing, painless fusion in a functional positionPresence of inflammatory arthritis, such as rheumatoid arthritis, systemic lupus erythematosus–associated arthritis, or ankylosing spondylitisCognitive impairment, inability to comprehend study requirements, or anticipated poor complianceAny other condition that, in the judgment of the investigator, renders the patient unsuitable for study participation

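### A fixed block size of 4 with unblinded surgeons can make up to a third of a site's allocations predictable, so the article's concealment claim is too strong

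*Protocol article*

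**What the plan says.** The protocol article, under Randomization and Blinding, states that randomization is done by the coordinating center "using a centralized computer-generated system with permuted blocks of 4 to ensure balanced allocation across treatment groups". It adds: "Assignment details will be distributed to all participating sites via sequentially numbered, sealed opaque envelopes". The same section says that "operating surgeons cannot be blinded because of the distinct intraoperative workflows".

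Under Recruitment Strategy and Patient Screening, patients are found eligible, informed, consented and enrolled. Then: "They will then be assigned to treatment groups according to the site’s randomization scheme". That section also refers to an electronic system: "After entering the electronic randomization system, all subject data will be locked". How this system relates to the envelopes is not explained.

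The exclusion criteria end with any other condition that, "in the judgment of the investigator, renders the patient unsuitable for study participation". Strengths and Limitations then claims: "Prospective randomization with concealed assignment minimizes selection bias".

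**The concern.** A sealed opaque envelope hides the next assignment from sight but does not stop anyone from working it out. With one known block size and equal allocation, whoever has followed the earlier cases at a site knows the last assignment of every block and sometimes the one before it. The surgical team sees each assignment as it is used. Several eligibility decisions rest on judgment, and all of them come before randomization.

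If predictions influence who is enrolled and when, the arms may differ in fracture difficulty. The primary outcome counts every image from fracture reduction onward, and reduction is manual in both arms, so a fracture that is hard to reduce adds images whatever the technique. The article relies on the objectivity of the count to limit performance bias. Objectivity gives no protection against selection into the arms.

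**Working it through.** **Inputs**
- Block size 4, one fixed size (Randomization and Blinding).
- Equal allocation: "With a 1:1 allocation ratio between the 2 groups" (Sample Size).
- Means 32.2 (SD 5.2) and 15.2 (SD 3.7), margin 15.4, one-sided 0.025, power 0.80, 126 per group (Sample Size).
- Number of sites: not given, so taken as an assumption below.

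**The plan's own figure.** The article gives no predictability figure. Its sample size does reproduce. The excess over the margin is 32.2 − 15.2 − 15.4 = 1.6, and the pooled variance is (5.2² + 3.7²)/2 = 20.365. The normal formula gives 2 × 20.365 × (1.96 + 0.842)² / 1.6² ≈ 125 per group. The t test gives 126 (power 0.8005), as stated. Predictable allocation does not change this figure; the issue is possible bias, not power.

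**Blocks within site, observer knows the block size and all earlier assignments there.** There are 6 equally likely sequences of two and two.

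| Position | Probability that it is certain | Probability that the best guess is right |
|---|---|---|
| 1 | 0 | 1/2 |
| 2 | 0 | 2/3 |
| 3 | 2/6 = 1/3 (first two agree) | 1/3 × 1 + 2/3 × 1/2 = 2/3 |
| 4 | 1 | 1 |
| Sum | 4/3 | 2.833 |

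- Certain share: (4/3)/4 = 33.3%.
- Best guess right: 2.833/4 = 70.8%.

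**One list shared across k equal sites, each site seeing only its own cases.** Position 3 is certain if both earlier cases were at the same site and agree: 1/(3k²). Position 4 is certain if the two matching earlier cases were both at that site: 1/k². The average over four positions is (1/(3k²) + 1/k²)/4 = 1/(3k²). That is 8.3% for k = 2 and 1.3% for k = 5. Simulation gave 8.3% and 1.3%.

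**Alternative block schemes within site.** Fixed sizes were enumerated. Mixed sizes were simulated over lists of 300, for an observer who knows the set of sizes but not their order.

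| Scheme | Certain | Best guess right |
|---|---|---|
| Fixed 4 | 33.3% | 70.8% |
| Fixed 6 | 25.0% | 68.3% |
| Fixed 8 | 20.0% | 66.6% |
| Mixed 4, 6 | about 5% | about 69% |
| Mixed 4, 6, 8 | about 2% | about 68% |

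Mixing nearly removes the certain allocations but lowers guessing accuracy only slightly.

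**The case against.** The strongest reply is that predictability in principle is not predictability in this trial. Stratification of the list by site is never stated, nothing says that sites were told the block size, and the article does not say that enrollers are the surgeons. This stands, and it makes the one-third figure an upper figure under stated conditions. The shared-list reading is possible, but it fits poorly with envelopes sent to sites and with assignment by a site's scheme.

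A second reply is that assignment already follows consent and formal enrollment, with a data lock and audit trails. This deserves credit: it limits changes after the assignment is known. It does not stop a prediction made before the patient is approached. The wording also leaves open whether the lock comes before the assignment is revealed.

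A reader might infer three stronger things that the article does not support:
- **That publication exposes about 100 of 300 patients.** Participant Compensation carries an exchange rate dated June 15, 2026, and enrollment is due to end by October 2026, so publication comes late. Assuming uniform accrual over about 28 months with 3 to 4 months left, 300 × 3/28 ≈ 32 to 300 × 4/28 ≈ 43 patients remain. A third of these is about 11 to 14. Earlier exposure would require sites to have known or inferred the block size.
- **That the bias favors navigation.** No passage suggests which fractures would be steered to which arm; either direction is possible. The screening window of day −7 to 0 also limits deferral. The 1.6-image excess over the margin shows sensitivity to any bias and does not estimate this one.
- **That envelopes contradict the electronic system.** A system that generates the list and logs enrollment can coexist with envelopes that deliver assignments. The relation is unexplained, which is a lesser fault.

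**Conclusion.** The concern holds in conditional form. A single block size of 4, delivered in sequential envelopes to sites with unblinded surgeons and judgment-based eligibility, is open to deduction. Up to 33.3% of a site's allocations are certain in advance and 70.8% are guessed correctly, provided that blocks run within site and enrollers know or infer the block size and the earlier allocations. On a shared list the certain share is about 8% with 2 equal sites and about 1% with 5, both site numbers being assumptions.

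Opaque envelopes alone do not support the unqualified claim in Strengths and Limitations that selection bias is minimized. The article gives no evidence that steering has occurred and no basis for the direction or size of a bias. The sample size is unaffected.

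**What to change.** 1. **Remaining patients.** Release each assignment from the electronic system only after consent and eligibility are locked. Use randomly varying block sizes within site (for example 4, 6 and 8), not disclosed to sites. State how the envelopes relate to the electronic system and whether the list is stratified by site. Central release matters as much as the block sizes, because mixing alone leaves guessing accuracy at about 68%.
2. **All randomized patients.** Add a sensitivity analysis that compares baseline Garden grade and the treatment effect on fluoroscopy count between determined and undetermined block positions. Block position is known from the list, and Garden classification is already collected at screening (Table 2).
3. **Text.** Qualify the concealment claim in Strengths and Limitations.

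The cost is some reprogramming, withdrawal of unused envelopes and slightly larger possible imbalance within sites. The first step reaches few patients because accrual is nearly complete, so the second is the main gain.

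The second step has limited precision. With all 300 analyzed, one third in determined positions and the planning SDs, the standard error of the difference in treatment effect is √[(5.2² + 3.7²)/50 + (5.2² + 3.7²)/100] = √(0.815 + 0.407) ≈ 1.1 images. That is a 95% half-width of about 1.96 × 1.1 ≈ 2.2 images. Undetermined positions can also be partly guessed. A null result would therefore be reassuring but would not prove that no steering occurred.
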